
#### Intervention Group

The intervention will commence from the induction of general anesthesia and continue until 4 hours after surgery. Ringer lactate (2 ml/kg/h) will be commenced upon admission to the OR to satisfy maintenance fluid requirements. CO and stroke volume index (SVI) will be measured by one of 2 CO monitors: (1) FloTrac system (Edwards Lifesciences Corp), which attaches to the arterial line already in place in this surgical population; or (2) Starling SV system (Cheetah Medical), a noninvasive CO monitor that utilizes 4 stickers placed on the patient’s trunk. No more than 500 ml of intravenous fluid will be administered at anesthesia induction. In addition to the maintenance fluid described previously, patients will receive 250 ml fluid challenges with crystalloid as required until they are no longer fluid-responsive. Albumin 5% will also be allowed for fluid challenges at the discretion of the attending anesthesiologist. The absence of fluid responsiveness will be defined as the absence of a sustained rise in SVI of at least 10% for 20 minutes or more, at which point the patient will be considered fluid-optimized. At this point, a low-dose dobutamine infusion at a fixed rate (2.5 μg/kg/min) will be commenced and maintained until 4 hours postoperatively. The infusion rate will be halved and/or discontinued if the patient develops tachycardia (heart rate ≥100 BPM) for more than 30 minutes despite adequate anesthesia/analgesia and fluid status (based on the aforementioned intervention). Further fluid challenges will be performed by the attending anesthesiologist with the aim of maintaining maximal SVI throughout the case. Postoperatively, the patient will remain in the postanesthetic care unit (PACU) for a minimum of 4 hours (as per the current standard of care), after which the CO monitoring and the dobutamine infusion will be discontinued and the patient transferred to a level 2 step-down critical care unit. Ringer lactate at 2 ml/kg/h will be infused to satisfy maintenance fluid requirements until oral fluid intake is permitted by the surgical team, at which point the maintenance infusion will be stopped. Data collection and follow-up for such patients will be performed as per the standard of care.

#### Control Group

Patients in the control group will also receive a baseline infusion of Ringer lactate at 2 ml/kg/h to satisfy maintenance fluid requirements, which will commence upon admission to the OR. The anesthetic management will otherwise be according to standard practice. This will include 250 ml fluid challenges with a crystalloid administered at the discretion of the attending anesthesiologist, generally guided by pulse rate, arterial pressure, urine output, and/or core-peripheral temperature gradient. Albumin 5% will also be allowed for fluid challenges at the discretion of the attending anesthesiologist. No specific CO monitoring device will be used to guide fluid therapy; however, it will be present in the OR throughout the case to ensure adequate blinding of the surgical team and research staff regarding the 2 patient groups. Likewise, perioperative dobutamine will not be used unless clinically indicated to improve cardiac function, as it is not currently part of our standard practice in these surgeries, and there is no yet documented evidence to support its use in all DIEP flap patients. We expect this study to address this knowledge gap and provide evidence as to whether there is a benefit to using it routinely. Postoperative care will be similar to the intervention group (except for the CO monitoring and dobutamine infusion in PACU).

#### Inclusion and Exclusion Criteria

The inclusion and exclusion criteria for patient recruitment are outlined in Textbox 1.

Inclusion and exclusion criteria for the study recruitment.
**Inclusion criteria**
Between 18 and 80 years of ageMeet the American Society of Anesthesiologists (ASA) physical status classification I-IIIUndergoing elective unilateral/bilateral immediate or delayed deep inferior epigastric perforator (DIEP) flap surgeryCognitive ability to provide informed consent
**Exclusion criteria**
Have dementia or neurological impairmentScheduled for DIEP flap combined with any other secondary surgical procedureDocumented left ventricular dysfunction (ejection fraction < 40%)Contraindication to low-dose dobutamineBMI <18 or >40 kg∙m-2Pregnant or lactatingRenal insufficiency, with an estimated glomerular filtration rate (eGFR) <30 ml/min/1.73m2)Known liver insufficiency (ie, documented cirrhosis, coagulopathy, and/or encephalopathy of hepatic origin)

#### Premature Withdrawal and Discontinuation Criteria

One of the limitations of dobutamine infusion is tachycardia. The infusion rate will be halved and/or discontinued if a patient develops tachycardia (heart rate ≥100 BPM) for more than 30 minutes despite adequate anesthesia/analgesia and fluid status (based on the aforementioned intervention). If the reduced dose does not correct the tachycardia, the infusion will be turned off. In addition, if at any point the attending staff raises concerns about the patient being at an increased risk because of study participation, the intervention will be stopped and the patient removed from the investigation. Moreover, if the patient decides they want to withdraw their consent at any point prior to publication, they will be excluded from the study and none of the information collected from them will be used for research purposes. The study intervention only applies during surgery and potentially for up to 4 hours postoperatively. All study participants will be fully monitored for the duration of the study intervention and beyond for up to 48 hours postoperatively. They will have immediate access to any additional care or intervention if required.

If patients are withdrawn from the study, we will continue to enroll consecutively until we have met our stipulated sample size of 20 patients per group. For patients who are withdrawn, we will seek permission to retain any data collected (especially demographic information) for comparison between those who were not and those who were withdrawn to determine whether they differ in any respect.

#### Rescue Medication and Risk Management

All anesthesia and surgical procedures are according to the standard of care except for the low-dose dobutamine infusion intraoperatively and potentially up to 4 hours postoperatively, the use of CO monitoring to guide fluid administration intraoperatively and for up to 4 hours postoperatively, and noninvasive measurements of tissue oxygenation until 48 hours postoperatively. Patients will be intensively monitored, and medications will be administered as considered medically necessary. Conversely, no medications deemed medically necessary will be withheld because of study participation. The main potential side effect associated with dobutamine is tachycardia. To mitigate this risk, our protocol proposes a very low-dose infusion. In addition, the dobutamine infusion rate will be halved and/or discontinued if the patient develops tachycardia (heart rate ≥100 BPM) for more than 30 minutes despite adequate anesthesia/analgesia and fluid status. Additionally, all patients will be intensively monitored while in the hospital for any adverse events/complications, which will be carefully considered in terms of whether they are related to the study intervention or otherwise and action will be taken accordingly.

#### Adverse Event Reporting

Adverse events and serious adverse events (SAEs) will be monitored and documented. Study staff will mandatorily report all SAEs to the investigator for evaluation as soon as they become aware. All adverse events will be immediately and mandatorily reported to the Queen’s University and Affiliated Teaching Hospitals Research Ethics Board and the Therapeutic Products Directorate of Health Canada, as per current guidelines.

If a patient experiences an adverse event due to study participation, medical care will be provided to them until resolution of the problem. Patients will be asked about satisfaction with healing and overall surgical care on the day of discharge. Patients will also receive a 30-day follow-up telephone call from research staff inquiring about complications and patient satisfaction.

#### Statistical Analysis

Data will be entered into REDCap (Research Electronic Data Capture; version 10.6.12; Vanderbilt University). Upon study completion, the data will be exported to SPSS software (version 29.0; IBM Corp) for analysis. Descriptive analyses, including mean, SD, median, and interquartile range for continuous data, as well as frequencies and percentages for categorical data, will be completed for all demographic and surgical characteristics and study outcomes. The underlying distributions of all continuous data will be assessed for normality using the Shapiro-Wilk test. Tissue oxygenation will be compared using independent sample *t* tests if the data are normally distributed and the Mann-Whitney *U* test in the event that they are not. Secondary outcomes will be compared between the 2 groups using the Fisher exact or Pearson chi-square tests (as appropriate depending on cell sizes) for categorical data and independent samples *t* tests (or the Mann-Whitney *U* test depending on the underlying distribution) for continuous data. Intent-to-treat analyses will not be conducted, and no adjustments will be made for missing data. Repeated measures analysis of variance (ANOVA), with the group as a factor, will be used to compare the tissue oxygenation over time (baseline, 1, 2, 4, and 8 hours postoperatively, along with baseline and postoperative day 1 and day 2 data). *P*<.05 will be used as the criteria for statistical significance, and no adjustment will be made for multiple comparisons. The possibility of a type I error will be acknowledged, and the actual *P* values will be presented for all comparisons.

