### Objectives and Outcome Measures

The main objective is to determine whether the use of minimally invasive CO monitoring to guide intravenous fluid administration, combined with low-dose dobutamine infusion (via a treatment algorithm), will increase overall tissue oxygenation in patients undergoing DIEP flap surgery. The primary outcome is tissue oxygenation, measured via near-infrared spectroscopy (NIRS), 45 minutes following vascular reanastomosis of the DIEP flap within the perfusion zone farthest from the perforator vessels. This zone is the most vulnerable surgical area to ischemia and therefore the most likely to reflect the potential benefits of the proposed intervention. In the case of bilateral DIEP flaps, this zone will be assessed in both the left and right breasts. The zonal blood supply for DIEP flaps is depicted by Holm (Figure 2) [21]. Zone 1 includes the perforator vessel and is thus the most reliably perfused portion of the flap, while any flow across the midline can be less reliable than ipsilateral flow depending on the location of the perforators in zone 1. As aforementioned, the primary outcome will be tissue oxygenation within the zones farthest from the perforator vessels.

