**Figure 2 figure2:**
[figure not shown]
Depiction of the Holm perfusion zones [21]. Zone I is well recognized for being the most richly perfused as it contains the perforator vessels. The use of this zone during deep inferior epigastric perforator (DIEP) flap breast reconstruction surgery may provide optimal tissue flap perfusion.

Our secondary outcomes include (1) tissue oxygenation at baseline (preoperatively), intra-operatively and 1, 2, 4, 8 hours postoperatively, as well as the morning of postoperative days 1 and 2; (2) the amount of intravenous fluids (crystalloids, colloids, blood products) and vasopressors (eg, phenylephrine, ephedrine, norepinephrine, etc) administered intraoperatively and up to 4 hours postoperatively; (3) the need for intraoperative surgical vascular reintervention (ie, reanastomosis); (4) laboratory measures including perioperative pH, serum lactate, and hemoglobin measures; (5) incidence of postoperative nausea and vomiting; (6) hospital length of stay; (7) any postoperative complications including infection, hematoma, and those resulting from flap malperfusion (ie, partial/total flap loss and fat necrosis); (8) the need for postoperative intervention for flap-related issues; (9) overall patient satisfaction; and (10) days alive and out of hospital, all up until 30 days postoperatively.

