#### Approved Protocol

A tissue oximeter device (SnapshotNIR; Kent Imaging) will be used for all patients. This is a portable noninvasive monitor that measures tissue oxygen saturation using NIRS technology with the capability of saving images to allow for subsequent analyses. Measurements will be taken by holding the monitor at a standardized (30 cm) distance from the skin area where the oxygen levels are to be measured. Upon admission to the OR, preoperative baseline measurements (with patients breathing ambient air without supplemental oxygen) will be recorded over the abdominal flap tissue, followed by recordings immediately postinduction, 1-hour postinduction, when the abdominal flap is free (and still perfused by the chosen perforator arteries), before clamp removal postarterial reanastomosis, and 45 minutes following reanastomosis. All research personnel dedicated to this study will receive prestudy training on the perfusion zones and study outcomes to ensure that oxygenation measures are consistently taken from the same surgical region in relation to the perfusion zones (as described in Figure 2) throughout each case. In addition, the surgical team, led by authors [name], will assist with guiding the intraoperative oxygenation measurements with respect to flap location. However, the surgical team and attending anesthesiologist will be blinded to the Kent oxygenation measurements throughout the perioperative period, and surgery will be guided as per the standard of care. The ischemic period during which the flap is transferred (reflected by a fall in the oxygen saturation of the flap [23]) as well as the time of flap revascularization (characterized by increased oxygen saturation [23]) will be recorded. Upon completion of the surgical procedure, another NIRS-based monitor (Somanetics INVOS 5100C Cerebral/Somatic Oximeter; Medtronic) may be applied to the freshly reconstructed graft at the surgeon’s discretion. If deemed appropriate, a sticker will be applied over the flap for continuous graft oxygenation monitoring up to 48 hours postoperatively. However, if the surgeon requires the entirety of the graft to be exposed for visual monitoring (as per the standard care), a sticker/sensor will not be applied. Nevertheless, postoperative measures will be routinely recorded at 1, 2, 4, and 8 hours postoperatively, as well as on the morning of postoperative days 1 and 2 using the Kent device. All measures will be consistently taken at the same location [24]. Note that continuous intraoperative monitoring with the Somanetics INVOS Oximeter is not possible, as the sensors cannot be sterilized.

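### The primary test leaves out the baseline oxygenation the trial already records, and a normality pre-test decides which hypothesis is tested

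*Protocol article*

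**What the plan says.** All places are in the protocol article.

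- **Endpoint** (Objectives and Outcome Measures): "The primary outcome is tissue oxygenation, measured via near-infrared spectroscopy (NIRS), 45 minutes following vascular reanastomosis of the DIEP flap", in the zone farthest from the perforators. It is a single post-treatment value, not a change.
- **Device and baseline** (Approved Protocol): "A tissue oximeter device (SnapshotNIR; Kent Imaging) will be used for all patients". With it, "preoperative baseline measurements (with patients breathing ambient air without supplemental oxygen) will be recorded over the abdominal flap tissue". The section also intends readings to come from the same region, relative to the perfusion zones, throughout each case.
- **Primary comparison** (Statistical Analysis): "The underlying distributions of all continuous data will be assessed for normality using the Shapiro-Wilk test". Then "Tissue oxygenation will be compared using independent sample" t tests if the data are normal, and the Mann-Whitney U "test in the event that they are not". No covariate or change score is named.
- **Where baseline is used**: it is listed among the secondary outcomes ("tissue oxygenation at baseline (preoperatively), intra-operatively and 1, 2, 4, 8 hours postoperatively"), and it enters a repeated measures ANOVA that "will be used to compare the tissue oxygenation over time (baseline, 1, 2, 4, and 8 hours postoperatively", plus postoperative days 1 and 2. The 45-minute time point is not in that list.

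**The concern.** Two separate choices are fixed in the text.

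First, the trial has 40 patients and a preoperative reading on each by the same instrument, yet the primary comparison ignores it. Any stable difference between patients in tissue oxygenation stays in the error term. The only model that uses baseline does not cover the primary time point. The Sample Size section, by contrast, is built on increases in oxygenation (1.75 versus 0.50 kPa), so the quantity used for sizing and the quantity tested are not the same kind.

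Second, a t test concerns a difference in means and a Mann-Whitney U test concerns rank ordering. If a Shapiro-Wilk result on the outcome data selects between them, the primary hypothesis is not known until the data are seen. The Discussion says a positive result will be used to plan a large multicenter trial, and that planning needs one prespecified effect measure.

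**Working it through.** **1. The article's own figure.** Sample Size gives a difference of 1.75 − 0.50 = 1.25 kPa, SD 1.0, α 0.05 and power 80%. Two-sided testing is assumed, because the number of sides is not stated.

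n per arm = 2 × [(1.960 + 0.842) / 1.25]² = 10.05, rounded up to 11. The stated 11 reproduces. By the noncentral t distribution, power is 79.6% at 11 per arm and 97.1% at the planned 20 per arm.

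**2. Unadjusted test at 20 per arm.** The standard error is SD × √(2/20) = 0.316 SD, with 38 degrees of freedom. The difference detectable at 80% power is 0.909 SD. Power for a 0.7 SD effect (an illustrative value, not the article's) is 58%.

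**3. ANCOVA on baseline.** Let ρ be the correlation between baseline and the 45-minute value. It is not given, so a range is assumed. The variance of the treatment estimate, relative to the unadjusted one, is

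V = (1 − ρ²) × (1 + 1/36),

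where the second factor allows for chance baseline imbalance. There are 37 degrees of freedom. The detectable difference is close to 0.909 × √V.

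| ρ (assumed) | V | Detectable at 80% power | Power at 0.909 SD | Power at 0.7 SD |
|---|---|---|---|---|
| unadjusted | 1 | 0.909 SD | 80.0% | 58% |
| 0 | 1.028 | 0.922 SD | 78.9% | 57% |
| 0.3 | 0.935 | 0.880 SD | 82.5% | 61% |
| 0.5 | 0.771 | 0.799 SD | 89.0% | 69% |
| 0.7 | 0.524 | 0.659 SD | 97.2% | 85% |

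Confidence intervals are about 3%, 12% and 28% narrower at ρ = 0.3, 0.5 and 0.7. At ρ = 0.5 the gain is like having 20 / 0.771 ≈ 26 per arm.

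**4. Break-even.** V = 1 when ρ² = 1 − 36/37 = 1/37, so ρ = 0.164. Allowing for the lost degree of freedom, it is about 0.17. Below that, adjustment gains nothing.

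**5. A second covariate.** If laterality is added and explains no further variance, the detectable difference at ρ = 0.3 is 0.893 SD. Power at 0.7 SD is then 59% at ρ = 0.3 and 68% at ρ = 0.5. At ρ = 0.2 it is 57.1%, slightly below the unadjusted 57.8%.

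**6. The pre-test.** This was simulated with 10,000 trials of 20 per arm: Shapiro-Wilk at 0.05 in each arm, then the t test if both arms pass and Mann-Whitney U otherwise. Testing by arm is an assumption, since the article does not say whether arms are pooled.

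| Outcome distribution | Gate selects Mann-Whitney (no effect) | Type I error, two-stage | Power at 0.909 SD, two-stage | Power, t test alone |
|---|---|---|---|---|
| Normal | 10% | 5.3% | 79.6% | 79.7% |
| Left-skewed, beta(8,2) | 48% | 5.7% | 81.7% | 79.9% |
| Lognormal | 77% | 5.7% | 90.1% | 80.6% |

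The simulation error on a 5% rate is √(0.05 × 0.95 / 10,000) = 0.22 points. The 5.3% is therefore within noise of 5%, while 5.7% is a small but real excess.

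**The case against.** The strongest points on the other side are these.

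- **The unadjusted test is valid.** This stands. Randomization protects it, and chance baseline imbalance is already reflected in its standard error. A reader might infer that the primary result would be biased; the article does not support that.
- **The correlation may be low.** This stands, and it limits the size of the gain. Baseline is taken on room air on the intact abdomen; the outcome is read on a transferred, reanastomosed flap under anesthesia. No figure in the article supports 0.5 or 0.7.
- **A same-zone baseline is not assured.** This stands in part. The same region is intended throughout, but zones are defined by the perforators, and the baseline is described only as over the flap tissue. A less well matched baseline lowers ρ; it does not make adjustment invalid.
- **Power is already 97% at the planned effect.** This is correct arithmetic but limited comfort. That effect comes from oxygen partial pressure at 8 hours in another trial, and Sample Size concedes that the groups are not identical.
- **The pre-test does little harm to power.** This stands. A reader might infer that the gate wastes precision or that its result is mostly chance. The simulation shows essentially no power loss and, under skewness, a gain over the t test. With normal data the switch occurs in only about 10% of trials; the near coin flip appears under one assumed skewed shape.
- **Estimates are promised.** This stands. A reader might infer that only P values will be reported, but Statistical Analysis also commits to means, SDs, medians and interquartile ranges for the study outcomes. A mean difference and its interval can be rebuilt from those.

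**Conclusion.** The point holds as an efficiency recommendation plus a call to fix the hypothesis in advance. It does not show that any planned result would be invalid.

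Leaving out baseline costs precision if ρ exceeds about 0.17. The loss is small at 0.3 (detectable difference 0.91 versus 0.88 SD), worthwhile at 0.5 (0.80 SD) and large at 0.7 (0.66 SD). If ρ is zero, adjusting costs about 1 power point. These figures assume a two-sided 5% test, one baseline covariate, one value per patient and complete data on 20 per arm. Because ρ is unknown, the size of the benefit is uncertain; the asymmetry between likely gain and worst-case cost is not.

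The precision loss comes from omitting baseline, not from the pre-test. The fault of the pre-test is that the data decide whether means or ranks are compared, with a slight rise in type I error under skewed outcomes.

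**What to change.** Before unblinding, amend the Statistical Analysis section as follows:

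1. Name one primary analysis: ANCOVA of 45-minute tissue oxygenation on group, with the preoperative baseline as covariate, reporting the adjusted mean difference with its 95% CI.
2. Treat laterality as an optional covariate, at the cost of one more degree of freedom. It does not settle how the two readings of a bilateral patient become one value, so state that rule as well.
3. State which preoperative reading serves as baseline, matched to the primary zone where the saved images allow it.
4. Remove the Shapiro-Wilk gate. Give a rank-based or permutation test as a sensitivity analysis regardless of the normality result.

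The cost is analysis wording and one degree of freedom, or two with laterality. The baseline reading is already planned for every patient, so no extra measurement is needed. The article reports that investigators were still blinded when it was written; if that remains so, the change can be made without knowledge of the results.

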#### Surgical Procedure

Patients will be marked in the preoperative holding area for an abdominal-based free-flap breast reconstruction. All procedures are planned as a DIEP reconstruction. For most flaps, the goal is to include 1 to 3 perforators to optimize perfusion. In some cases, the DIEP flap may be converted to a muscle-sparing flap to achieve adequate arterial inflow and venous outflow to the tissue flap. Because the primary outcome is to look at perfusion of the flap most distant from the perforating vessels, in most cases, unilateral breast reconstructions will be performed, and perfusion zones 1, 2, and 3 included, according to the Holm classification (Figure 2). However, in patients with bilateral reconstructions, only Holm zones 1 and 2 will be included in a single flap. The supplying deep inferior epigastric vessels will be harvested at the level of the iliac artery and vein, and a microvascular anastomosis will be performed with the internal mammary artery and vein under a surgical microscope. A single artery and vein will be routinely anastomosed.

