
All surgical procedures will be performed by one of the 2 surgeons ([name]) to minimize variability in patient selection and surgical technique, both predictors of clinical outcomes in microsurgery [25]. Elective DIEP flap surgical procedures and anesthetic management will be completed in accordance with the standard of care. Perioperative management will be identical in both groups, apart from the hemodynamic monitoring for guiding intravenous fluid therapy and interventions as described below. In the OR, the ambient temperature will be set at 20^o^ C and standard monitors will be applied. Invasive monitoring in the form of an arterial line will be established as per the current practice. General anesthesia will be induced with propofol and fentanyl, followed by rocuronium to facilitate endotracheal intubation, and maintained with end-tidal sevoflurane (Et_sevo_=1.5%-3%) and additional doses of fentanyl and/or hydromorphone administered at the discretion of the attending anesthesiologist. Extra doses of rocuronium will be administered throughout the case for muscle relaxation. A mean arterial pressure (MAP) ≥65 mmHg will be targeted throughout the perioperative period. Likewise, all patients will receive standard measures to maintain oxygen saturation (SpO_2_ ≥95%), end-tidal carbon dioxide (Et_CO2_) between 35 and 40 mmHg, hemoglobin (>8 g/dl), and a heart rate <100 beats per minute (BPM). A warming device (enFlow IV Fluid/Blood Warming System; GE Healthcare) will be used for intravenous fluids, along with a forced-air patient warming system (Bair Hugger Normothermia System; 3M) to maintain normothermia (core temperature between 36 and 37.5 ^o^C). Arterial blood gasses will be checked every 2 hours (or more often at the discretion of the attending anesthesiologist) to specifically monitor the pH, SpO_2_, partial pressure of oxygen (PaO_2_) in arterial blood, partial pressure of carbon dioxide (PaCO_2_) in arterial blood, base excess, hemoglobin, and lactate levels as surrogates for tissue perfusion perioperatively. Urine output will be recorded hourly. The total amount of vasopressor, perioperative fluid (crystalloids and albumin 5%), and blood products, if any, will be recorded. In addition, the following demographic and surgical characteristics will be included: age, BMI, preoperative hemoglobin and hematocrit levels, American Society of Anesthesiologists (ASA) classification, Charlson Comorbidity Index, and total surgical and anesthetic time. Subsequently, 4 mg prophylactic intravenous dexamethasone upon the induction of general anesthesia and 4 mg ondansetron 15 minutes prior to completion of the surgical procedure will be administered to prevent nausea and vomiting. All patients will be managed postoperatively in a high-dependency unit (level 2 critical care) and given an intravenous patient-controlled analgesia (IV-PCA) pump containing hydromorphone (or an alternative in the case of adverse reactions) for postoperative pain management, as per the current standard of care. The postoperative goals (up to 48 hours postoperative) will be similar to the intraoperative period, namely: MAP ≥65 mmHg (or within 20% of baseline), SpO_2_ ≥95%, PaCO_2_ between 35 and 45 mmHg, hemoglobin >8 g/dl, core temperature between 36 and 37.5 °C, and heart rate <100 BPM. Research personnel will call patients 30 days postoperatively to document any complications, hospitalizations, and overall satisfaction. If patients cannot be reached via telephone, the patient’s family physician may be contacted and their medical record accessed to determine whether the patient experienced postoperative complications or required medical attention (as per the informed consent form).

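### The primary comparison is fixed without a surgeon term although two surgeons operate; the test is valid, but a two-level surgeon factor specified before unblinding would be a cheap gain in robustness

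*Protocol article*

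**What the plan says.** The Statistical Analysis section sets the test: "Tissue oxygenation will be compared using independent sample" t tests if a Shapiro-Wilk check supports normality, and the Mann-Whitney U "test in the event that they are not". Neither branch has a covariate.

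Under Approved Protocol, "All surgical procedures will be performed by one of the 2 surgeons", and the stated reason is "to minimize variability in patient selection and surgical technique, both predictors of clinical outcomes in microsurgery". The list of demographic and surgical characteristics in that section does not include surgeon. The Background section names the same two factors among those that may contribute to perfusion-related complications.

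Under Surgical Procedure, some choices are made during the operation: "For most flaps, the goal is to include 1 to 3 perforators to optimize perfusion", and a flap may be converted to a muscle-sparing one.

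On the measurement, Approved Protocol says that the surgical team "will assist with guiding the intraoperative oxygenation measurements with respect to flap location". It also sets safeguards: research staff are trained "to ensure that oxygenation measures are consistently taken from the same surgical region in relation to the perfusion zones", and "the surgical team and attending anesthesiologist will be blinded to the Kent oxygenation measurements throughout the perioperative period".

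Study Design, Randomization, and Blinding describes computer-generated allocation of 40 patients, 20 per group, and names no stratification factor.

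**The concern.** The protocol gives its own reason to think that the operator matters, and it reduces operator variation by using only two surgeons. Any difference that remains between those two goes into the error term of the stated test. If one surgeon's patients also fall unevenly between the arms, part of that difference enters the treatment estimate. With 40 patients there is little room to average this out.

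Patients are approached at a preoperative visit with the surgeon, so surgeon is probably settled before allocation and known for every patient. It is an easy variable to use.

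**Working it through.** **Inputs from the documents.** 20 per group; α 0.05, SD 1.0, power 80%, 11 per arm, and rises of 1.75 and 0.50 kPa, so a difference of 1.25 kPa (Sample Size). Sidedness is not stated.

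**The plan's own figure.** n = 2(1.96 + 0.8416)² × 1.0² / 1.25² = 10.05, rounded up to 11 per arm. This reproduces two-sided; one-sided gives 8. Noncentral-t power at 11 per arm is 79.6%. At 20 per arm, power for 1.25 SD is about 97%.

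**Inputs assumed.** The documents give neither a surgeon effect on oxygenation nor a caseload split. I take surgeon to explain a share R² of the variance (5%, 10% or 20%) and 20 cases per surgeon. With equal caseloads, the surgeon difference in within-surgeon SDs is √(4R²/(1 − R²)) = 0.46, 0.67 or 1.0.

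**Precision.** The standard error in total-SD units is √(2/20) = 0.316, with 38 df. The difference detectable with 80% power is 0.909 SD. With a surgeon term the residual SD is √(1 − R²), with 37 df:

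| R² | Detectable difference (SD) | Power at 0.909 SD | Equivalent extra patients, 40/(1 − R²) − 40 |
|---|---|---|---|
| 0 | 0.910 | 79.9% | 0 |
| 5% | 0.887 | 82% | 2 |
| 10% | 0.863 | 84% | 4 |
| 20% | 0.814 | 88% | 10 |

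The table assumes that surgeons are evenly split between arms. With an uneven split, the adjusted variance is divided by 1 − φ², where φ is the arm-surgeon correlation. Unstratified allocation gives a mean φ² of 1/39. Putting that in, the four powers become 78.9%, 80.9%, 83.0% and 87.1%, about one point lower each.

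**Chance imbalance.** If surgeon is not used in the allocation, the hypergeometric distribution (40 patients, 20 per surgeon, 20 per arm) gives a 12 v 8 split or worse with probability 34%, 13 v 7 or worse 11%, and 14 v 6 or worse 2.6%. If the caseload is 70/30, the chance that one surgeon's cases differ between arms by 4 or more is 30%, and by 6 or more 8%.

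**Effect of an imbalance.** At 13 v 7, a 0.5 SD surgeon difference moves the unadjusted estimate by (13/20 − 7/20) × 0.5 = 0.15 SD, or 0.15/0.316 = 0.47 of a standard error. In simulation with the split fixed at 13 v 7, the t test rejects a true null in about 7%, 9% and 11% of trials for surgeon differences of 0.5, 0.8 and 1.0 SD.

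**Validity overall.** Averaged over all allocations, simulated type I error is 4.9% with a surgeon difference of 0.5 or 1.0 SD. The excess at uneven splits is offset at even ones.

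**The case against.** The strongest reply is that nothing here is wrong. No stratification factor is named, so an unadjusted test contradicts nothing in the design. Its standard error already allows for chance imbalance, and type I error holds. This stands, and it limits the point to efficiency and robustness. A reader might infer that the primary result would be biased or invalid; the documents do not support that. What remains is conditional: the sponsor will analyse one allocation, and at an uneven one the error rate can exceed 5%.

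Second, the textual support is indirect. The predictor statement concerns clinical outcomes, not oxygen saturation at 45 minutes, and it explains a mitigation. The Background section narrows that gap by tying the same factors to perfusion, but only as a possibility. No section says that these two surgeons differ.

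Third, a reader might infer from the surgical team's help in locating the reading that the site varies by surgeon. The trained staff, the same-region aim and the blinding to readings weigh against that. They do not address operative technique.

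Fourth, power is already about 97% at the planning values. That is correct, but those values are cutaneous oxygen pressure at 8 hours, whereas the primary outcome is a near-infrared reading at 45 minutes. The margin may not carry over.

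Fifth, the baseline reading, or unilateral versus bilateral surgery, has at least as good a claim as a covariate. That is fair: surgeon is not shown to be the most important one. It is not a reason to leave it out.

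Last, this is a condensed article, so silence on stratification does not prove that there is none. The unadjusted test, however, is stated outright.

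**Conclusion.** The point holds as a worthwhile improvement. The primary comparison is fixed without surgeon, although the protocol's own text makes surgeon a plausible source of variation. The gain runs from nothing if the surgeons do not differ to about 2, 4 or 8 points of power at the 80% benchmark, for an assumed 5%, 10% or 20% of variance explained. It is about a point less once average chance imbalance is counted. Protection against an uneven split is the second benefit.

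These sizes rest on an assumed surgeon effect and, mostly, on equal caseloads; the documents give neither. That precision is in fact being lost cannot be concluded from them.

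**What to change.** Before unblinding, state in the Statistical Analysis section:

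- The primary analysis is a linear model of the 45-minute reading on arm, with surgeon (two levels) as a fixed factor. Report the adjusted difference with its 95% CI.
- For the primary outcome this model replaces the Shapiro-Wilk switch. If residuals are clearly non-normal, a rank-based or permutation test stratified by surgeon is the sensitivity analysis.
- Each patient contributes one value. In bilateral cases, where both breasts are read, this could be the mean of the two flaps.
- The unadjusted test is kept as supportive.

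Add surgeon to the surgical characteristics listed under Approved Protocol.

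No new patients are needed, and the only added variable should already be in the operative record. The statistical cost is one degree of freedom: about 0.1 point of power if surgeon has no effect and the split is even, and about one point averaged over unstratified allocation. The larger cost is procedural. The Results section reports 34 participants completed with investigators still blinded, so the change comes late and must be dated and documented as made while blinded. If unblinding has already taken place, the adjusted model can only be reported as a sensitivity analysis.
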